## Data analysis

The study is based on the intention-to-treat principle. SPSS 28.0 will be used for data analysis. First, to ensure comparability after randomization, we will compare the differences between the groups at the baseline. The continuous variables will be analyzed by a t-test when the data have a normal distribution, and non-normally distributed data will be analyzed using the Mann-Whitney U test. Baseline differences between groups in terms of sociodemographic and clinical variables will be assessed using Chi-square tests for categorical variables and an analysis of variance (ANOVA) for continuous data. To compare intervention effects, a mixed-effect regression model will be used. Group (BAPT or BA) will be used as an inter-subject factor, and time (baseline, post-treatment, and follow-up) as an intra-subject factor. We will utilize Cohen's d to achieve both the intra- and intergroup analyses. P < 0.05 was set as statistically significant.

Financial Support

This study was supported by Science and Technology Program of Guangzhou (grant No. 205171098044), Guangzhou Municipal Key Discipline in Medicine (2021-2023), Guangzhou High-level Clinical Key Specialty, and Guangzhou Research-oriented Hospital.

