
At the baseline, week 2 (the end of the basic intervention), week 4 (the end of all the high-order intervention), week 8, and week 16, participants from the two groups will be evaluated with the corresponding scales to assess the degree of depression, behavioral activation level, non-suicidal self-injury behavior, and sleep quality scores. We will also calculate the improvement of symptoms for each dimension in each group at each time point, and then compare the divergences between the two groups. All participants will receive an electronic exercise wristband as a reward after they completed the follow-up.

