## Statistical analysis

### Sample size calculation

The depressive symptom scores of the study subjects will be used as the main outcome index, with a bilateral α = 0.05 and a 90% confidence interval. In a previous study on the effects of BA combined with traditional exercise therapy, the depression scores of the intervention group at the baseline and at the 16-week follow-up period were 27.3 ± 8.0 and 16.0 ± 9.5, respectively[46]. Therefore, we expect that the depression score of the experimental group in the present study could be decreased by 11.3 points compared with the baseline and 4.8 points compared with the control group. We used PASS 15 software to calculate the sample size of the experimental group: N1 = N2 = 84. Considering the expectation that 10%­–20% of the cases will be

lost during the period following the study, the number of participants needed in the intervention group and control group will be about 100, respectively.

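### The mixed model puts baseline MADRS in a three-level time factor with no baseline covariate, although five visits are collected; adjusting for baseline would be at least as precise at no cost

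*Protocol*

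**What the plan says.** The Data analysis section of the protocol names a mixed-effect regression for the intervention effect and describes its factors: "Group (BAPT or BA) will be used as an inter-subject factor, and time (baseline, post-treatment, and follow-up) as an intra-subject factor". It names no baseline covariate and does not say which term or time point carries the primary comparison. Baseline is otherwise dealt with by significance tests: "First, to ensure comparability after randomization, we will compare the differences between the groups at the baseline".

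The Synopsis and the Efficacy evaluations section schedule five assessments: baseline, week 2, and then "week 4 (the end of all the high-order intervention), week 8, and week 16". Efficacy evaluations also makes MADRS from week 0 to week 16 the primary outcome, and says that improvement will be worked out for each group at every assessment and then compared between groups.

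The Sample size calculation takes its scores from an earlier study, where those of the intervention group "at the baseline and at the 16-week follow-up period were 27.3 ± 8.0 and 16.0 ± 9.5, respectively". It expects the score to be "decreased by 11.3 points compared with the baseline and 4.8 points compared with the control group", works "with a bilateral α = 0.05 and a 90% confidence interval", and arrives at 84 per arm before dropout.

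**The concern.** Three things in the stated model do not sit well with the rest of the protocol.

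1. The visits do not match the time factor. Week 2 falls in the middle of a four-week course, so it is neither baseline, nor post-treatment, nor follow-up. Weeks 8 and 16 share a single label. A three-level factor cannot deliver the comparison at each assessment that Efficacy evaluations promises.
2. Baseline is a response rather than a covariate. The treatment effect then depends on which term is read. The group-by-time contrast is a comparison of changes, and its variance depends on how strongly baseline and follow-up scores correlate. The group main effect averages in a baseline difference that is zero in expectation under randomisation.
3. The baseline tests do not fill the gap. A significance test after randomisation cannot secure comparability and does not adjust the estimate.

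At stake is power that depends on an unstated correlation and on an unnamed model term, when baseline scores already being collected could remove that dependence.

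**Working it through.** **Inputs.** From the Sample size calculation: difference 4.8; SD 8.0 at baseline and 9.5 at 16 weeks; two-sided α = 0.05; 84 evaluable per arm. Two inputs are inferred. The section speaks of a 90% confidence interval, read here as 90% power, and it does not say which SD was used. The baseline-to-follow-up correlation ρ is not given, so results are shown over a range. All powers below use the noncentral t distribution with 84 per arm.

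**The plan's own figure.** A two-sample t-test with difference 4.8, SD 9.5 and 90% power needs exactly 84 per arm; power at 84 is 0.902. With SD 8.0 the answer would be 60. So 84 fits an unadjusted comparison of week-16 scores.

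**(a) Group-by-time contrast, follow-up minus baseline.** The expected difference is 4.8 − 0 = 4.8. The variance is 8.0² + 9.5² − 2ρ(8.0)(9.5), so SD = √(154.25 − 152ρ). It equals 9.5 when ρ = 8.0/(2 × 9.5) = 0.42. Below that value the contrast is less precise than the sample size assumes; above it, more precise.

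**(b) Baseline-adjusted week-16 difference.** The expected difference is 4.8 and SD = 9.5√(1 − ρ²), which never exceeds 9.5.

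**(c) Group main effect over the three levels**, with the effect present at both later levels and equal correlation ρ between levels. The estimate is (0 + 4.8 + 4.8)/3 = 3.2. The variance of a participant's mean is [8.0² + 9.5² + 9.5² + 2ρ(76 + 76 + 90.25)]/9 = (244.5 + 484.5ρ)/9.

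| ρ (assumed) | (a) SD | (a) power | (b) SD | (b) power | (c) SD | (c) power |
|---|---|---|---|---|---|---|
| 0.2 | 11.13 | 0.79 | 9.31 | 0.91 | 6.16 | 0.92 |
| 0.3 | 10.42 | 0.84 | 9.06 | 0.93 | 6.58 | 0.88 |
| 0.42 | 9.50 | 0.90 | 8.62 | 0.95 | 7.06 | 0.83 |
| 0.5 | 8.85 | 0.94 | 8.23 | 0.96 | 7.35 | 0.80 |
| 0.7 | 6.92 | 0.99 | 6.78 | 0.995 | 8.05 | 0.73 |

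**(a) against (b).** The difference in variance is (154.25 − 152ρ) − 90.25(1 − ρ²) = 64 − 152ρ + 90.25ρ² = (8.0 − 9.5ρ)². This cannot be negative, so the change contrast is never more precise than the adjusted comparison. The gap is largest where ρ is low and has almost closed by ρ = 0.7.

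**(a) against (c).** The two unadjusted readings move in opposite directions. Reading (a) reaches 90% only from about ρ = 0.42 upwards, and reading (c) only up to about ρ = 0.25. No single ρ protects both.

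**The case against.** The strongest reply is that a repeated-measures model with baseline as a response level is valid and common, provided the group-by-time contrast is what is tested. The protocol leans that way: it speaks of changes from week 0 to week 16 and of improvement compared between groups. On that reading nothing is diluted. With ρ above about 0.42 the analysis is more precise than the sample size assumes, because the sample size takes no credit for baseline at all. This stands.

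It is also fair to say that the three labels may be shorthand for phases, since all five visits are listed elsewhere. That weeks 8 and 16 would be pooled and week 2 dropped is an inference; no sentence says so. If the factor in fact has five levels, even the main-effect dilution is milder: 4.8 × 4/5 = 3.84, with the effect at all four later visits.

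Finally, the interaction term, covariance structure and visit coding are commonly left to a statistical analysis plan, which is not at hand. Their absence is not held against the protocol here. What remains is what the text does state: three levels that include baseline, beside five visits and a comparison at each of them.

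A reader might go further and infer that the planned analysis must either dilute the effect or be less precise than the sample size assumes. The documents do not support that. The dilution needs a test of the group main effect, which the protocol never names, and the loss against the sample size needs ρ below about 0.42, a value the protocol does not give.

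**Conclusion.** The point holds in a limited form. The stated time factor does not match the visit schedule or the promised per-visit comparison. A model that keeps baseline as an unconstrained outcome level also gives up precision relative to one that adjusts for it. Against the change contrast, adjustment raises power at 84 per arm from 0.84 to 0.93 at ρ = 0.3 and from 0.94 to 0.96 at ρ = 0.5; at ρ = 0.7 the gain is negligible. The shrinkage to 3.2 is a risk only if the main effect is later reported as the treatment effect.

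These figures rest on 90% power and SD 9.5 being the inputs behind 84, on SDs of 8.0 and 9.5 in both arms, on an assumed ρ, and for (c) on equal correlations and an effect already present after treatment. The conclusion that adjustment is never less precise than the change contrast, and never below the inferred 90%, does not depend on the value of ρ.

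This is a should-fix. The baseline significance tests are a minor blemish: they neither bias the estimate nor cost power.

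**What to change.** In the Data analysis section, replace the three-level time factor with the actual post-baseline visits (weeks 2, 4, 8 and 16) as a categorical factor. Include arm, arm-by-visit and baseline MADRS as a covariate, or keep baseline as a response with its mean constrained equal across arms. State that the treatment effect is the adjusted arm difference at week 16, which is the quantity that reproduces the sample size. As a tidy-up, replace the baseline significance tests with a descriptive table.

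The cost is a few sentences. No additional data, visits or participants are needed. The change should be made before anyone sees outcome data by arm, so that the choice between readings is not open afterwards.
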